##### Secondary objective(s)

The secondary objective is to reduce craving in offenders with substance abuse problems. This will be assessed using the four self-report measurements on alcohol and drug craving, and to compare the results from pre-test to post-test. Other study parameters are the results from the self-report questionnaires. These will be compared with the other variables mentioned before and also compared from pre-test to post-test.

#### Instruments

##### Passive-viewing empathy task

To measure empathic abilities and how it changes between pre and post intervention, patients will participate in a passive-viewing empathy task. This measurement is based on previous research [72]. The pictures used in the passive-viewing task are selected based on ratings conducted through an anonymous online study (i.e. Amazon’s Mechanical Turk): 188 individuals participated in this study and each individual rated 45 pairs of pictures. These were aggression pictures and matched neutral pictures; both were rated on levels of arousal, aggressiveness, and valence. The study resulted in 40 pairs of pictures selected for the empathy tasks. The pictures display scenes with either two men, or one man and one woman aged between 20 and 25 years old. The men have a white complexion and the woman has a black skin tone. The majority of the aggression pictures (99%) had a male perpetrator and either a male or a female victim. The scenes involved physical, sexual, and verbal aggression. To control for stimulus-related confounding factors, all neutral pictures are carefully matched to the aggressive pictures. The neutral photographs were identical to the aggression-related photographs (pair-wise, i.e. the same persons, same location, same colors, same light), only without the aggressive action. Three types of pictures will be used in the experiment: (1) 40 pictures displaying an interaction between two individuals that is of a violent tone; (2) 40 pictures displaying an interaction between two individuals that is neutral, and (3) fifteen pictures displaying neutral objects like a bridge or a lamp (fillers). The fillers will not be used for further analyses: 95 pictures in total will be randomly presented for 6 s each, with intervals of 1.8 s between the pictures. Participants are instructed to look at each picture passively, because then the automatic neural response in the brain can be determined [72].

##### Rating empathy task [72]

Following the passive viewing empathy task, the pictures displaying the neutral and aggressive situations will be presented a second time. Participants are now instructed to rate the pictures by answering four questions. The first question is “Does this picture give you arousal?”. This is assessed to score arousal on a 9-point Likert scale (1 = no arousal to 9 = very high arousal). The following question was to assess the valence of the picture: “Does this give you a negative or a positive feeling?” This is assessed on a 9-point Likert scale (1 = negative emotions, 5 = no emotions, 9 = positive emotions). The last two questions assess the measure of state empathy. Last, there are two questions concerning empathy (i.e. measure of state empathy). One question assessed to what extent the participant could empathize with the perpetrator and the other question assessed to what extent the participants could empathize with the victim in the aggressive situations. Both questions will be scored on a 9-point Likert scale (1 = no empathy to 9 = high empathy). The total empathy task (passive viewing and rating) on average lasts 40 min [71].

##### The Point Subtraction Aggression Paradigm (PSAP)

Although multiple paradigms are used to measure aggression on an experimental manner in the laboratory, the PSAP task is known to be one of the best-validated instruments [88]. During the PSAP task participants play a game against a (fictive) opponent. The goal of the game is to earn more points than your opponent. Participants are offered 3 choices: (1) participants can earn points by pressing 100 times on the “1” button on the keyboard; (2) stealing points from your opponent by pressing ten times on the “2” button; or (3) guarding your own points as an escape so the opponent cannot steal from you by pressing ten times on the “3” button. When a participant picks option number 2 (aggressive response), the points that they steal will not add up as their own score, but will only be subtracted from the score of the opponent. If the (fictive) opponent is stealing points from the participants, this will be shown in red letters on the screen; in this way the participant will be “provoked”. If this provoking leads to the participant pressing the “2” (stealing) button more frequently, this can be seen as reactive aggression. When the participant is not provoked by this event, the aggression can be seen as proactive aggression. In this study the e-prime version of the PSAP consists of three 12-min sessions. The outcome of the PSAP, the aggressive response, is the number of “2” responses made by the participant. When the “2” response is a result of the provocation (the fictive opponent stealing points), then this indicates a reactive aggression response. If the “2” response is not a reaction to the provocation, then the reaction will be seen as proactive aggression response. Research [88] concludes that the PSAP has more ecological validity then for example the Taylor Aggression Paradigm (TAP) [89]. This is due to the following advantages: first, the PSAP task offers the participant an option to actively withdraw (pressing the “3” key), something that is not included in other paradigm tasks. Second, in the PSAP task the aggressive response (pressing the “2” button) is not receiving points and therefore is more ecologically valid then other tasks that do not have this option. An aggressive reaction is a cost-benefit consideration, so choosing an option to steal points that will not add up to your own score for winning could be considered as a costly option.

#### Self-report questionnaires

##### Self-Report Psychopathy Scale Short-Form (SRP-SF)

We use the Dutch short version of the SRP-SF [90] in order to assess psychopathic traits. The SRP-SF consists of a subset of 29 of the 64 original items and is a self-report questionnaire in which participants are asked to rate statements using a 5-point Likert scale. The questionnaire consists of four subscales: interpersonal manipulation (manipulation and deception), callous affect (lack of empathy or regret), instable lifestyle (impulsivity and sensation-seeking behavior) and criminal behavior (delinquency and criminal behavior).

##### Reactive and Proactive Aggression Questionnaire (RPQ)

We use the Dutch version of the RPQ [91] in order to assess aggression. The RPQ is a 23-item self-report questionnaire in which the participant has to give a rating based on how often this behavior has occurred in the past, on a 3-point scale (“never”, “sometimes”, or “often”). Next to an overall total aggression score, the test provides two separate measures of proactive aggression (deliberate and planned aggression) and reactive aggression (aggression as a reaction to an unplanned circumstance).

##### Interpersonal Reactivity Index (IRI)

We use the Dutch version of the IRI [92] in order to assess empathy. This is a commonly used self-report instrument designed to assess empathic tendencies. The IRI consists of four separate subscales: perspective taking (PT), fantasy (FS), empathic concern (EC), and personal distress (PD).

##### Toronto Alexithymia Scale (TAS-20)

We use the Dutch version of the TAS-20 [93] in order to assess alexithymia. The TAS-20 is a self-report scale comprising 20 items. Each item is rated on a 5-point Likert scale ranging from 1 (strongly disagree) to 5 (strongly agree). The TAS20 is a reliable and valid measure of emotion processing in adults that includes a total score and three subscales: difficulty identifying feelings (DIF), difficulty describing feelings (DDF), and externally-oriented thinking (EOT).

##### Risky, Impulsive, and Self-Destructive Behavior Questionnaire (RISQ)

We use the Dutch version of the RISQ 96] in order to assess risky and impulsive behavior. The RISQ is a 38-item self-report questionnaire-based measure, assessing eight domain-specific factors (measuring drug use, aggression, self-harm, gambling, risky sexual behavior, impulsive eating, heavy alcohol use, and reckless behavior).

##### Behavioral Impulsivity Scale (BIS-11) [94]

We use the Dutch version of the BIS-11 [94] in order to assess the personality and behavioral construct of impulsivity. The BIS-11 is a questionnaire that consists of one of the three second-order facets of impulsivity. The 30-item self-report questionnaire consists of six subscales: attention (i.e. focusing on current tasks), cognitive instability (i.e. intruding thoughts), motor impulsiveness (i.e. acting quickly), perseverance (stable lifestyle), cognitive complexity (i.e. enjoys mental challenges), and self-control, (i.e. plans and thinks deliberatively).

##### Alcohol Use Disorders Identification Test (AUDIT)

We use the Dutch version of the AUDIT [95] in order to assess alcohol use. The 10-item AUDIT includes questions to assess alcohol intake (questions 1–3), alcohol dependence (questions 4–6), and alcohol-related problems (questions 7–10). Questions 1–8 are scored from 0 to 4, questions 9 and 10 are scored 0, 2, or 4, resulting in a maximum AUDIT score of 40.

##### Drug Use Disorder Identification Test (DUDIT)

We use the Dutch version of the DUDIT [96] in order to assess drug use. The DUDIT is an 11-item screening instrument to assess non-alcohol drug use patterns and various drug-related problems. The first nine items are assessed on a 5-point Likert scale and the last two items are scored on a 3-point scale. Higher scores suggest more severe drug problems.

##### Obsessive Compulsive Drug Use Scale (OC-DUS-version Cocaine)

We use the Dutch version of the OC-DUS [97] in order to assess drug craving. The OC-DUS version Cocaine is a 13-item self-report questionnaire that assesses the inability to control or resist cocaine-related thoughts and behaviors, frequency and impact of thoughts and impulses related to cocaine use, and the degree of interference.

##### Obsessive Compulsive Drinking Scale (OCDS)

We use the Dutch version of the OCDS [98] in order to assess alcohol craving. The 22-item Dutch version of the OCDS was developed to reflect obsession and compulsivity related to craving and drinking behavior. The OCDS has been shown to be specific for the obsessive and compulsive characteristics of drinking-related thought, urges to drink, and the ability to resist those thoughts and urges in alcohol-abusing and alcohol-dependent individuals.

### Outcomes

#### Primary outcomes

The primary outcomes are empathic abilities, aggressive behavior, and the electrophysiological response in the brain. Empathic abilities will be measured using the Passive Viewing Empathy Task [72], followed by the Rating Empathy Task [72]. The Passive Viewing Empathy task examines the electrophysiological outcomes of empathic processing while observing aggressive situations. The results will be measured in the amplitude of specific ERPs. The early ERP component resembles the P300, which is a positive voltage in the latency of 300–650 ms and the late ERP component reflects the late positive potential (LPP), a sustained positive potential identified at around 400–1000 ms. Specifically, P3 and LPP appear to be a measure of empathic processing, and therefore make EEG an adequate tool to indicate any change in empathic abilities, reflected as a change in the amplitude of the ERPs [73]. In the Rating Empathy Task [72] the pictures displaying the neutral and aggressive situations will be presented a second time. Participants are now instructed to rate the pictures by answering four questions that will result in an outcome in emotional valence, empathy for the perpetrator, empathy for the victim, and arousal. The outcome of the self-reported assessment of empathy is used to measure state empathy.

Aggressive behavior will be assessed using the PSAP task. The PSAP task is known to be one of the best-validated instruments in provoking aggression in the laboratory [88]. In this task the participants will be “provoked” by a (fictive) opponent who will steal points from them. If the (fictive) opponent is stealing points from the participants, this will be shown in red letters on the screen. If this provoking leads to the participant pressing the “2” (stealing) button more frequently, this can be seen as reactive aggression. The results of the PSAP task will be the amount of pressing the “2” button in proportion to the total amount of pressing the buttons.

As a standard for effectiveness of the reduction of violent behavior next to the PSAP, the results of a violence risk assessment instrument (HKT-R) [78] will be assessed before the intervention starts. The HKT-R is one of the mandatory risk-assessment tools in forensic institutions. The clinical, historical, and future indicators of violent behavior and the risk of recidivism will be used as the outcome for the reduction of violent behavior.

Functional brain changes will be measured using rsEEG, with a resting-state task to measure the baseline of the brain activity of the participant in a resting-state condition and the passive viewing empathy task to measure the electrophysiological changes in brain function during empathic induction caused by the intervention. The expectation is that patients who receive tDCS will show higher event-related potential (ERP) towards the pictures of the victims after the intervention compared with patients who have receive the sham condition.

After 6 months, as a standard for effectiveness of the reduction of violent behavior, the results of the aggression task (PSAP) and the risk-assessment tool (HKT-R) will be compared to the results obtained before the intervention. The HKT-R risk level will be obtained to see whether there is a longitudinal effect of tDCS on aggression and risk reduction. In addition, to check whether the effect of the tDCS intervention is long-lasting, the participants will complete the self-report questionnaires, the empathy task, and the aggression task once more.

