### Statistical analysis

Different general linear models (GLM) in SPSS will be used to analyze the main parameters. For instance, analyzing the empathy and aggression outcome (empathy ratings and b responses in the PSAP task), the outcome variables will be handled as the dependent variables. In addition, the group variable (active versus sham) will be used as the independent between-group variable, whereas the pre-post time will be included as a within-subject independent variable. A mixed design will be used in which the pre-post intervention in the experimental group will be compared with the pre-post intervention aggression outcomes in the sham group. The mixed design will be used for the PSAP outcomes, empathy ratings, self-report questionnaires, and assessment of risk of violence with the HKT-R instrument.

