### Power analysis

The sample size is based on the primary outcome and other studies from the aforementioned guidelines [76] and seen as achievable. The sample size is based on research [100] that reported large effect sizes (i.e. partial eta squared 0.25 and 0.21) for the active versus sham condition, using 15 participants per condition for three conditions. Because we have two experimental conditions but also include covariates, a sample size of 50 subjects (25 per condition) is considered to have enough power to detect an effect, when power is set to 80% and alpha of 5%, two sided.

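### Three unranked primary outcomes, covering about seven to nine variables, sit beside a sample size built on one unnamed primary outcome, and nothing shown says which result meets the objective

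*Protocol article*

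**What the plan says.** The Primary outcomes section opens with "The primary outcomes are empathic abilities, aggressive behavior, and the electrophysiological response in the brain". The three are listed side by side, with no order and no lead variable. Under them the section places:

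- two ERP components: "Specifically, P3 and LPP appear to be a measure of empathic processing";
- a rating task, with participants "answering four questions that will result in an outcome in emotional valence, empathy for the perpetrator, empathy for the victim, and arousal";
- the aggression task: "Aggressive behavior will be assessed using the PSAP task";
- the HKT-R risk assessment, as a further standard for reduced violence;
- resting-state EEG, for functional brain changes.

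The Power analysis section speaks in the singular: "The sample size is based on the primary outcome and other studies". It does not name that outcome. It gives the only significance level in the article: "when power is set to 80% and alpha of 5%, two sided".

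The Statistical analysis section says "Different general linear models (GLM) in SPSS will be used to analyze the main parameters", and describes a group-by-time mixed design for the PSAP, ratings, questionnaires and HKT-R. The abstract and the Primary objective section build the main question on empathy and violence, and bring in EEG as an additional question.

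**The concern.** A reader cannot tell from the article whether the trial has one primary outcome, two or three, or which variable stands for each. Nor does it say whether one, all, or one per domain must be positive before tDCS is said to have met its objective. With 25 patients per arm and several candidate variables, that leaves room to choose the primary result after the data are seen.

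Two further inconsistencies widen that room. The PSAP section defines the outcome as the number of aggressive responses, but the Primary outcomes section defines it as their share of all button presses. The Overview of procedure expects scores on both the aggression and the empathy task to fall after treatment, while the stated aim is to increase empathy.

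**Working it through.** **The plan's own figure.** Inputs from Power analysis: partial eta squared 0.25 and 0.21, two-sided 5%, 80% power, 25 per arm. With f = √(η²/(1−η²)) and d = 2f for two equal groups:

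- η² = 0.25: f = 0.577, d = 1.15; a t test needs 13 per arm.
- η² = 0.21: f = 0.516, d = 1.03; a t test needs 16 per arm.

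This does not reproduce 50, but 50 exceeds the need, and the section cites covariates and guidelines without a formula. With 25 per arm, power for one test at 5% is 98% or 95%. So the sample size is adequate for one outcome at the assumed effects, and it is not the defect here.

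**Counting the variables.** Two ERP components + four ratings + PSAP + HKT-R + resting-state EEG = 9. The Rating empathy task section says only the last two questions measure state empathy. Dropping valence and arousal gives 2 + 2 + 1 + 1 + 1 = 7. One variable per domain gives 3.

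**Chance of at least one false positive when there is no effect.** Two assumptions are needed that the article does not state: each variable is tested at two-sided 5%, and any one significant result counts as success.

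Independent tests: 1 − 0.95^m.

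- m = 9: 1 − 0.6302 = 37.0%
- m = 7: 1 − 0.6983 = 30.2%
- m = 3: 1 − 0.8574 = 14.3%

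For a common correlation ρ between test statistics, the rate is 1 − ∫[Φ((c − √ρ·x)/√(1−ρ)) − Φ((−c − √ρ·x)/√(1−ρ))]^m φ(x)dx, with c = 1.96. The article gives no correlations, so a range is shown:

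| Tests | ρ = 0 | ρ = 0.3 | ρ = 0.5 | ρ = 0.7 |
|---|---|---|---|---|
| 9 | 37.0% | 32.6% | 26.9% | 20.2% |
| 7 | 30.2% | 27.1% | 23.0% | 17.8% |
| 3 | 14.3% | 13.6% | 12.5% | 10.9% |

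With nine variables correlated at 0.3 to 0.7 within domains and 0 or 0.2 between domains, simulation gives 28% to 35%.

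**What control would cost in power.** A fixed sequence tests each step at the full 5%, so the first test keeps the 98% or 95% above. For comparison, Bonferroni over three domains (0.05/3 = 0.0167) gives 94% or 87%, and over nine variables (0.05/9 = 0.0056) gives 87% or 77%, at the two assumed effects.

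**The case against.** The strongest reply is that the article never says each outcome is tested at 5%, and never says that any single success is enough. The only significance level belongs to the sample size. The Primary objective section joins its two aims with 'and'; if both empathy and aggression had to be positive, the error rate would not be inflated at all. A multiplicity procedure may also sit in a full protocol or analysis plan that is not shown. All of this stands. The missing procedure is therefore not a finding in itself, and the percentages are conditional.

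The count can also be challenged. Valence and arousal may not be intended as empathy outcomes. HKT-R is scored before treatment and at six months, so it falls outside the pre-test to post-test comparison that defines the primary objective. A reader might push the count to 13 by splitting the PSAP into reactive and proactive responses and the HKT-R into its three indicators, but the article states no separate primary tests of these.

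A reader might also infer that the overlap between the P300 (300–650 ms) and LPP (400–1000 ms) means the same signal is counted twice. The article gives component latencies, not scoring windows or electrode sites, so that does not follow.

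What the reply does not remove is the disagreement in the text. Which outcome is primary is addressed in the abstract, Primary objective, Primary outcomes and Power analysis, and the answers differ. An analysis plan could add an alpha rule; on its own it could not make those sections agree.

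**Conclusion.** The point holds as an inconsistency about what is primary and what would count as success. Three unranked domains with about seven to nine variables are set against one unnamed primary outcome in the sample size, and EEG has a different standing in different sections.

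If every variable were tested at 5% and any one success were enough, the false-positive chance would be 37% for nine independent tests, about 33% to 20% at assumed correlations of 0.3 to 0.7, 30% for seven independent tests, and 11% to 14% for one test per domain. A reader might infer that the trial carries a one-in-three chance of a false primary claim. The documents do not support that as a flat statement, because neither condition is written down and the correlations are assumed.

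**What to change.** Before unblinding, and by a dated amendment, make the abstract, Primary objective, Primary outcomes and Power analysis agree:

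- Name one variable per domain and state its direction of benefit.
- Test the three in a fixed sequence at two-sided 5%. One order that follows research questions 1, 2 and 4 is the victim-empathy rating of aggressive pictures, then PSAP aggressive responding, then one pre-named ERP amplitude. The choice of order is the sponsor's.
- Report perpetrator empathy, arousal, valence, the other ERP, resting-state EEG, HKT-R and the reactive/proactive split as secondary or exploratory.
- Use a single PSAP definition, either count or proportion.
- Reconcile the expected fall in empathy-task results in the Overview of procedure with the aim to increase empathy.

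No extra patients or measurements are needed. There are two costs. A later outcome in the sequence cannot be claimed as confirmatory if an earlier one fails. And because the trial is registered and has been recruiting since February 2019, the change must be openly recorded as made during the trial.

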#### Secondary outcomes

Beside the primary outcomes, the current study distinguishes multiple secondary outcomes. These will be measured using the self-report questionnaires described in the 'Instruments' section. All the secondary outcomes will be assessed during T0 and again at T6.

